#### Pressure pain threshold testing

Pressure pain threshold (PPT) testing will be conducted using a pressure algometer (FDN200, Wagner Instruments, USA) with a probe area of 1 cm^2^, which exerts pressures of up to 200 N/cm^2^/2000 kPa. The PPT is determined using an ascending stimulus intensity (slowly increasing ramps of 50 kPa/s (~ 0.5 kg/cm^2^s) applied bilaterally over the three test sites: the affected joint (knee, assessed over the tibial below the medial joint line), an unaffected joint (ipsilateral proximal radioulnar joint), and over the thenar eminence. The study participant is asked to notify the examiner as soon as the sensation becomes painful, and the pressure exerted recorded. The PPT is determined by the mean of the threshold from a series of three stimulus intensities each applied as a slowly increasing ramp of 50 kPa/s [51].

#### OMERACT–OARSI responder criteria

Response to krill oil will be assessed using the OMERACT–Osteoarthritis Society International (OARSI) set of response criteria [41]. Participants will be classed as responding if they have high improvement in pain (using the VAS) or function (using WOMAC function scale) of ≥ 50% and absolute change ≥ 20; or if they have positive relative (≥ 20%) or absolute (≥ 10) change in two out of three of pain, function or patient’s global assessment.

#### Lower limb muscle strength

Lower limb muscle strength is a key correlate of pain and typically increases when pain reduces [52]. We will assess lower limb leg strength in both legs simultaneously, using a dynamometer (TTM Muscular Meter, Tokyo, Japan) as previously described [21]. This is done in duplicate and the mean of the two estimates is used. The muscles measured in this technique are mainly the quadriceps and hip flexors. The previously published repeatability estimate (Cronbach’s α) for this method is 0.91 [53].

#### Measure of intermittent and constant osteoarthritis pain

Intermittent and constant osteoarthritis pain (ICOAP) is a multidimensional OA-specific measure designed to comprehensively evaluate the pain experience in people with hip or knee OA. This includes pain intensity, frequency, and impact on mood, sleep and quality of life, independent of the effect of pain on physical function [54], over the past 7 days. It contains 11 items in two domains with two supplementary items on intermittent pain predictability, and uses rating scales with five categories of response, e.g., “not at all,” “mildly,” “moderately,” “severely,” and “extremely” [54]. Each ICOAP item is scored from 0 to 4; missing data are dealt with according to rules in the user guide [55]. Scores are produced for each subscale separately by summing subscale scores for each item and then normalising each score from 0 (no pain) to 100 (extreme pain). The ICOAP is reliable (Cronbach’s α 0.93, ICC 0.85 [54]) and valid [54].

#### Quality of life

Quality of life will be assessed using the Assessment of Quality of Life (AQoL-6D) questionnaire, which assesses six separately scored dimensions (Independent Living, Relationships, Mental Health, Coping, Pain and Senses), each with variable item numbers and response levels [56]. The AQoL-6D has good psychometric properties [57]. Utility scores will be calculated based on methods published on the AQoL website [56] with a range 0–1 where 0 indicates the worst health state and 1 the best.

#### Blood samples

Fasting blood samples will be obtained from study participants at screening, 12 and 24 weeks. Samples will be analysed for fasting glucose, lipids (total, HDL and LDL) and hsCRP. The blood will be either tested fresh or stored at − 80 °C.

### Other assessments

#### Radiographs

A standing anteroposterior semiflexed radiograph of the ‘study’ knee will be performed at screening. X-rays will be scored for joint space narrowing and osteophytes on a four point scale (0–3) using the OARSI atlas [39]. In our hands this method has very high reproducibility with an ICC of 0.98 for joint space narrowing and 0.99 for osteophytes [58].

#### Anthropometry

These include height (stadiometer) and weight (electronic scales) and body mass index (BMI) (weight/height^2^) measured at weeks 0, 12 and 24.

#### painDETECT

Neuropathic pain will be assessed by the painDETECT questionnaire (− 1 to 38) at screening to provide information on level of nociceptive and/or neuropathic contributions to pain. A painDETECT score < 12 is defined as unlikely neuropathic pain, and 13–18 as possible neuropathic pain [59].

#### Concomitant medication

Use of pain medicines will be recorded by questionnaire at all visits. Participants will be asked to keep medications as stable as possible (including NSAIDs) and use paracetamol as rescue medication. Use of fish and krill oil during the trial will not be permitted, and use must cease 2 weeks prior to randomisation. Participants who commence anti-coagulant therapy will be withdrawn from the trial. We will assess analgesic use from the medication data.

#### Treatment guessing and adherence

Study participants will be asked what treatment they think they received at the 12- and 24-week assessments with the following options: krill oil, placebo, or not sure.

Adherence to treatment will also be assessed at the 12- and 24-week assessments by standard pill count methods [60].

#### Safety assessment

Adverse events will be monitored throughout the study. Standard safety and efficacy monitoring will be performed through regular face-to-face visits and phone calls between visits. The patients are requested to report any adverse events to the research staff spontaneously. Details of the adverse event and its relationship with study intervention will be recorded and reported to the local Human Research Ethics Committees in accordance with the requirements of individual committees.

### Sample size calculations

Using data from another trial conducted in our centre [52], assuming 10-mm difference between krill oil and placebo on the VAS pain scale (reduction in VAS pain scores in the placebo group by − 15.5 ± 25.5 mm over 12 weeks) and using assumptions of 90% power and 5% probability of type 1 error (alpha = 0.05), we will need 234 participants. Adjusting for 10% loss to follow-up, we need 260 participants (130 in each arm). Based on data on effusion-synovitis volume in our vitamin D RCT for knee OA, there was 13.7 ml (SD = 10.7) in the placebo group and 13.6 ml (8.1) in the active group (in those with effusion-synovitis at enrolment, i.e., 60%) at baseline [61]. With 234 subjects we will have 90% power to detect a difference of 4.5 ml. It is likely we will see at least a reduction of this amount with a treatment that effectively targets inflammation. What level reflects clinical significance is uncertain but this level is approximately 2.5 times the change that could be expected with measurement error. Furthermore, modelled data from our long-term Tasmanian cohort demonstrates that a reduction in effusion-synovitis size by 4.5 ml will decrease the need for joint replacement by 30% over 13 years (unpublished data).

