### Randomisation and blinding

Study participants were allocated to receive either krill oil or placebo in a 1:1 ratio based on computer-generated random numbers using a central randomisation website hosted by the University of Tasmania using adaptive allocation (minimisation) [40]. Briefly, the randomisation program examined the number of participants that were currently assigned to each of the two arms and then adjusted the randomisation thresholds so that the arm with the fewest participants would have a greater chance of being selected. Randomisation will be stratified by study site and is accessible by a dedicated website. This will be conducted by staff members with no direct involvement in the study.

The randomised controlled trial will be a double-blind one, with both patients and investigators assessing outcomes blinded to treatment allocation. Allocation concealment and double blinding will be ensured by: 1) use of identical softgels for each group; 2) objective measures of knee structural changes being made by trained observers blinded to group allocation; and 3) subjective measures being taken by research nurses blinded to group allocation.

Emergency unblinding will be allowed in limited situations that impact on the safety of study patients. Code-break for the full randomisation schedule will be maintained by the University of Tasmania. Patients who are unblinded will be withdrawn from treatment but will continue to be followed as per the planned follow-up schedule.

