### Statistical analysis

The primary analyses will be intention-to-treat analyses of primary and secondary outcomes. Per protocol analyses will be performed as the secondary analyses.

Changes in knee pain, knee effusion-synovitis size and any other outcomes which were collected using a linear scale will be analysed using a linear mixed model with treatment, month and their interaction (treatment × month) as covariates, as well as outcome measured at baseline and the baseline interaction with month. Incidence of adverse events will be assessed using log binomial regression. Correlated data within trial centres and the repeated measures will be addressed using trial centre and patient identification as random intercepts. Month will be treated as random effect to allow different treatment effects among patients over time. The sensitivity of models to the structure for the random effects and covariance structures will be assessed using likelihood ratio tests. Change in outcome measures within each group and differences in changes between groups from baseline to follow-up will be calculated using linear combinations of the estimated coefficients. If there are baseline imbalances in covariates between treatment groups, we will consider adjusting for them based on whether we regard the imbalance as clinically significant. Missing data caused by loss to follow-up and non-responses will be addressed by adding variables that have complete data at baseline and can explain missingness to the regression models.

Secondary analysis for missing data will be performed in people with full medication adherence (e.g., > 80% of softgels) and using imputation. Baseline variables with complete data will be used for data imputation assuming missing at random.

Subgroup analyses will be performed to examine which subgroups may respond better to treatment. These will include effusion size, radiographic knee OA, co-pathology present on MRI, pain characteristics, levels of inflammatory markers and serum lipid measures. Statistical significance will be set as a two-sided *P* value < 0.05.

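### The stated inputs for knee pain give 234 participants at 85% power, not the claimed 90%, which would need 274

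*Protocol article*

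**What the plan says.** The Sample size calculations section of the protocol article gives the pain calculation in two sentences.

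- Effect: "assuming 10-mm difference between krill oil and placebo on the VAS pain scale".
- Variability, from an earlier trial at the same centre: "reduction in VAS pain scores in the placebo group by − 15.5 ± 25.5 mm over 12 weeks".
- Error rates and result: "using assumptions of 90% power and 5% probability of type 1 error (alpha = 0.05), we will need 234 participants".
- Allowance for dropout: "Adjusting for 10% loss to follow-up, we need 260 participants (130 in each arm").

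Two further inputs stand elsewhere in the article. On the test, the Statistical analysis section says "Statistical significance will be set as a two-sided" P value below 0.05. On allocation, the Randomisation and blinding section says that participants were "allocated to receive either krill oil or placebo in a 1:1 ratio".

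The Sample size calculations section mentions no baseline correlation, no gain from repeated measures, and no separate pain SD for the krill oil arm.

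**The concern.** Every input to a standard two-sample calculation is on the page, and the result does not follow from them. The gap is 40 evaluable participants (274 − 234), which is too large for rounding or for the choice between the normal and t distributions.

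Pain is the first-named primary outcome, the 10 mm difference is the stated hypothesis, and this calculation fixed the trial size. If the power is 85%, the chance of missing a true 10 mm effect is 15% rather than 10%, half as large again. Readers of a null pain result may use the stated power to judge how firmly a 10 mm benefit has been ruled out, and the article would lead them to overrate it.

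**Working it through.** **Inputs.** Difference δ = 10 mm, SD σ = 25.5 mm, alpha 0.05 and power 90% (Sample size calculations); two-sided test (Statistical analysis); 1:1 allocation (Randomisation and blinding). Two readings are mine. The ± 25.5 is not labelled in the text and is taken as an SD. It is given for the placebo group only and is applied to both arms.

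**Formula.** n per arm = 2 × (z for alpha + z for power)² × (σ/δ)², with (25.5/10)² = 6.5025 and z = 1.960 for two-sided 0.05.

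| Power | z for power | n per arm | Rounded up | Total |
|---|---|---|---|---|
| 80% | 0.842 | 102.1 | 103 | 206 |
| 85% | 1.036 | 116.8 | 117 | **234** |
| 90% | 1.282 | 136.6 | 137 | **274** |

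The plan's 234 is reproduced exactly, but at 85% power. The noncentral t distribution gives totals of 208, 236 and 276, so the choice of distribution does not close the gap.

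**Power actually delivered.** The standard error with 117 per arm is 25.5 × √(2/117) = 3.334 mm. Then 10/3.334 − 1.960 = 1.039, which is a power of 85.1% (84.8% by noncentral t). With 130 per arm and no loss at all it is 88.5% (88.3% by t).

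**Difference detectable with 90% power at 117 per arm.** 3.2415 × 25.5 × √(2/117) = 10.8 mm.

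**SD that would make the claim true.** 10 / (3.2415 × √(2/117)) = 23.6 mm.

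**Other settings tried.** A one-sided 5% test at 90% power gives 112 per arm, 224 in total. That does not match 234, and the article specifies a two-sided test. A two-sided alpha of 0.025 at 90% power gives 324.

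**Dropout step.** 234/0.9 = 260, which is correct. The same step applied to 274 gives 304.4, so 305, or 306 with equal arms.

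**Effusion-synovitis volume, same section.** With 117 per arm and the placebo SD of 10.7 ml, the difference detectable with 90% power is 3.2415 × 10.7 × √(2/117) = 4.53 ml, against 4.5 ml stated (power 89.6% at 4.5 ml). So the plain two-sample formula with the placebo SD in both arms reproduces the volume statement at 90%.

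**The case against.** The strongest reply is that the planned analysis is not the unadjusted comparison used above. The Statistical analysis section specifies a linear mixed model that adjusts for baseline and uses the repeated pain measurements. If baseline and change correlate at about 0.38 in absolute value, the residual SD falls from 25.5 to 25.5 × √(1 − 0.38²) = 23.6 mm and power reaches 90%. A correlation of 0.3 would give 88% and one of 0.5 about 93%. This stands as a possibility: the power of the final analysis could be 90% or more. It does not rescue the sentence as written, because the article gives no correlation and the only SD it names for pain is 25.5 mm.

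A second reply is that 25.5 mm describes the placebo arm only. An SD of about 21.5 mm in the krill oil arm would bring the average variance down to 23.6² and the power to 90%. No such figure is given for pain, so this too would be an undisclosed assumption.

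Third, the volume calculation is imperfect support for the method. It reproduces only with the larger of the two SDs given (pooling 10.7 and 8.1 ml to 9.49 ml would give 95% power at 4.5 ml), and those SDs describe baseline values rather than change. That is fair. The finding on pain does not depend on the volume calculation.

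Finally, power stays above 80%, recruitment is over, and a null result should be judged mainly on its confidence interval. This limits the practical consequence. It does not make the stated power correct.

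**Conclusion.** The concern holds. From the inputs the article states, 234 evaluable participants give 85% power for a 10 mm difference in VAS pain, about 5 percentage points below the claim, and 90% would need 274. None of the sample sizes named in the article reaches 90% on those inputs. The exact match at 85% suggests that the power was mis-stated rather than that an undisclosed method was used, but the document cannot settle which.

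The conclusion rests on reading 25.5 mm as an SD common to both arms and on an unadjusted two-sided comparison. Adjustment for baseline could bring the power of the final analysis up to the claimed level, but only if the residual SD is 23.6 mm or less, which is nowhere stated.

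**What to change.** Restate the pain calculation: 234 evaluable participants (260 randomised) give 85% power to detect a 10 mm difference, assuming an SD of 25.5 mm in both arms and a two-sided alpha of 0.05, or 90% power to detect 10.8 mm. If the sponsor did rely on baseline adjustment or on a smaller SD in the active arm, say so and give the figure assumed. For an adjusted analysis the residual SD must be 23.6 mm or less.

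The cost is one sentence and a slightly less favourable power statement. No extra enrolment is asked for, and the analysis is unchanged. The trial report should carry the corrected figure.

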### Statistical analysis

The primary analyses will be intention-to-treat analyses of primary and secondary outcomes. Per protocol analyses will be performed as the secondary analyses.

Changes in knee pain, knee effusion-synovitis size and any other outcomes which were collected using a linear scale will be analysed using a linear mixed model with treatment, month and their interaction (treatment × month) as covariates, as well as outcome measured at baseline and the baseline interaction with month. Incidence of adverse events will be assessed using log binomial regression. Correlated data within trial centres and the repeated measures will be addressed using trial centre and patient identification as random intercepts. Month will be treated as random effect to allow different treatment effects among patients over time. The sensitivity of models to the structure for the random effects and covariance structures will be assessed using likelihood ratio tests. Change in outcome measures within each group and differences in changes between groups from baseline to follow-up will be calculated using linear combinations of the estimated coefficients. If there are baseline imbalances in covariates between treatment groups, we will consider adjusting for them based on whether we regard the imbalance as clinically significant. Missing data caused by loss to follow-up and non-responses will be addressed by adding variables that have complete data at baseline and can explain missingness to the regression models.

Secondary analysis for missing data will be performed in people with full medication adherence (e.g., > 80% of softgels) and using imputation. Baseline variables with complete data will be used for data imputation assuming missing at random.

Subgroup analyses will be performed to examine which subgroups may respond better to treatment. These will include effusion size, radiographic knee OA, co-pathology present on MRI, pain characteristics, levels of inflammatory markers and serum lipid measures. Statistical significance will be set as a two-sided *P* value < 0.05.

### Data integrity and management

Data will be recorded using case report forms and processed centrally at the Menzies Institute for Medical Research, University of Tasmania. The hard copies of case report forms will be stored in a locked area at each study site with secured and restricted access. The electronic data will be stored on password-protected servers with restricted access. All data collected will be kept strictly confidential. Daily backups of all electronic data will occur to minimise any risk of lost data. Data transfer will be encrypted with all data de-identified. Only members of the research team who need to contact study patients, enter data or perform data quality control will have access to patient information.

After study completion, paper copies of data will be archived in secure storage. Identifiers will not be removed in case follow-up of study patients is necessary; however, electronic data will continue to be kept in a secure electronic database. This will remain password protected and with access given only to the study investigators unless otherwise authorised by the study team.

### Withdrawal

If patients withdraw from the study before 6 months of follow-up, the reason and date will be recorded. An early MRI will be considered for participants who can not make the final visit.

### Roles and responsibilities and monitoring

The University of Tasmania (as the trial sponsor) and the principal investigators are responsible for all aspects of the trial, including design, conduct and oversight. The principal investigators will monitor the conduct and progress of the project at each site. The trial coordinator will visit each study site to make sure that all trial procedures are compliant with the trial protocol. The principal investigators and the research team will have regular teleconferences to ensure efficient study execution and ongoing monitoring of the study progress, with summary documents circulated after each meeting. Krill oil has a good safety profile [31] and is available over-the-counter, so we do not plan to use a data safety monitoring board. The trial is also being monitored at each site by a practicing rheumatologist.

### Dissemination plans

The results of this study will be presented at conferences and published in scientific journals. Any notes or publications arising from our research will be de-identified. Only aggregate statistical results will be presented.

The outcomes of the project will be disseminated to study patients using non-technical language. Dissemination of the overall study findings to the patients will occur in a de-identified manner and be based on the entire study population. The scientific paper will be available for dissemination to study participants.

## Discussion

We propose a multicentre, randomised, double blind placebo-controlled trial to determine whether krill oil 2 g/day improves knee pain and reduces size of knee effusion-synovitis compared to placebo in people with clinical knee OA, significant knee pain and knee effusion-synovitis. If krill oil proves effective, it will offer a novel therapeutic approach to reduce or slow progression of knee OA.

Krill oil is theorised to have an effect via both anti-inflammatory and anti-oxidative mechanisms. Oxidative stress and inflammation have important roles in OA pathogenesis and krill oil therapy may be beneficial in treating OA. Krill oil (300 mg/day) reduced inflammation (as measured by CRP) by 30% in 30 days vs 25% increase in patients receiving placebo [34]. This may have important clinical implications, with low level inflammation associated with increased loss of tibial cartilage volume (β = − 1.18% per annum per quartile of IL-6) [62]). Accordingly, trials are starting to use MRI-assessed effusion/synovitis as a treatment target. In a trial using low dose oral prednisolone for painful hand OA, MRI-assessed effusion-synovitis was associated with pain cross-sectionally, but not hand pain as assessed by VAS; however, effusions did not change over time with treatment or predict response to treatment [63].

Effusion and synovitis can also be assessed using ultrasound; such effusions predict knee replacements independent of severity of radiographic damage and pain [20]. Presence of ultrasound-detected knee effusions has been used to select people who might respond well to oral methotrexate, which demonstrated efficacy in an open-label trial, albeit without a control group [64]. However, the reproducibility of ultrasound is largely dependent on the operator and ultrasound is not yet well utilised in clinical trials of knee OA. This study will enable comparisons of MRI vs ultrasound indices in assessing change in effusion volume and provide evidence of which imaging modality is of most use in this context.

In summary, knee OA is a major but poorly understood public health problem with no pharmacologic therapies that affect disease progression. Two small trials [34, 35] suggest that krill oil will improve knee pain and may reduce systemic inflammation in people with OA. If krill oil can reduce knee pain and effusion size in knee OA, study findings will be readily translated into clinical practice as krill oil is already popular and available over the counter despite limited evidence of efficacy.

